### Study endpoints

The primary outcome variables are PPC and PCT kinetics. PPC are defined as new infiltrates or atelectasis on a chest X-ray, abnormal breathing sounds on auscultation, respiratory failure defined as PaO_2_/FiO_2_ < 300 or the need for noninvasive or invasive ventilatory support within the first three postoperative days. PCT kinetics will be evaluated during and after surgery. Blood samples will be taken at 0, 2, 6, 12, 24, 48 and 72 h after surgical incision. According to recent data it is expected that PCT values will peak at approximately 24 h after surgery and that they should decline by approximately 50% daily in the case of an uneventful postoperative course. Therefore, in addition to the absolute values the change between T_0_–T_24_–T_48_ will also be evaluated [16, 22].

Secondary outcome variables are extrapulmonary complications: incidence of circulatory failure, gastrointestinal and renal dysfunction, hematologic and coagulation disorders and infection (Table 1).

**Table 1 Tab1:** Secondary endpoints

Endpoint	Time frame	Detailed description
Circulatory failure	28 days	Hypotension – MAP < 65 mmHg
		Severe cardiac arrhythmia – 40/min < HR > 150/min
		ScvO_2_ < 70%
		dCO_2_ > 7 mmHg
		Serum lactate > 2 mmol/L
		Severe metabolic acidosis (actual bicarbonate < 18 mmol/L)
		Acute coronary syndrome
		Acute left ventricular failure
		Pulmonary embolism
		Cardiac arrest
Gastrointestinal dysfunction	28 days	Constipation
		Ileus
		Anastomotic leakage
		Reoperation
		Disorders of liver function
Renal dysfunction	28 days	RIFLE criteria
Hematologic and coagulation disorders	28 days	Severe bleeding
		Coagulopathy – INR > 1.5
Infection	28 days	Any infection except from pneumonia

*MAP* mean arterial pressure, *HR* heart rate, *ScvO*
_*2*_ central venous oxygen saturation, *dCO*
_*2*_ central venous-to-arterial carbon dioxide gap, *INR* International Normalized Ratio

Tertiary endpoints are intensive care unit (ICU) days, in-hospital stay, in-hospital and 28-day mortality.

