### Blinding, data collection, randomization and record-keeping

This is a single-blinded (participant) study. Patient data, intraoperative and postoperative measurements, fluid balance, respiratory parameters, laboratory results and clinical status (Sequential Organ Failure Assessment (SOFA) score) will be collected onto Case Report Forms (CRF). CRF and the patient evaluation chart will not be assessed in front of the patient.

Participants will be randomized to the SG or CG in a ratio of 1:1. Randomization will be carried out by a computer-generated blocked randomization list with 10 blocks of four patients per block. Allocation will be stored in sealed, opaque and numbered envelopes. Participants will be included and allocated in numerical order.

All original records (CRF and relevant correspondence) will be archived and secured for 15 years, and then destroyed according to the hospital standards concerning destruction of confidential information.

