### Selection of the participants

Patients with bladder cancer scheduled for open radical cystectomy and urinary diversion will be screened and recruited during routine perioperative assessment. Participants fulfilling the inclusion criteria will be asked for their signed informed consent. Withdrawal of consent may be initiated by the participant at any time during the trial.

Inclusion criteria are age over 18 years, patients with bladder cancer undergoing radical cystectomy and urinary diversion (ileal conduit or orthotopic bladder substitute) and provision of signed informed consent.

Exclusion criteria are age below 18 years, American Society of Anesthesiologists (ASA) physical status IV, history of severe chronic obstructive pulmonary disease (COPD, GOLD grades III or IV), history of severe or uncontrolled bronchial asthma, history of severe restrictive pulmonary disease, pulmonary metastases, history of any thoracic surgery, need for thoracic drainage before surgery, renal replacement therapy prior to surgery, congestive heart failure (NYHA grades III or IV), extreme obesity (Body Mass Index, BMI > 35 Kg/m^2^) and lack of patient’s consent.

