#### Postoperative care

After extubation, patients will be admitted to the ICU. ABGs and CVBGs will be collected and evaluated (pH, base excess (BE), standard bicarbonate (stHCO^3−^), ScvO_2_), PaO_2_/FiO_2_ and central venous-to-arterial carbon dioxide gap (dCO_2_) will be calculated every 6 h until 72 h after surgery. On the first postoperative day (POD), a chest X-ray will be performed and repeated on the following days if the development of pulmonary complications are suspected. The chest X-ray will be evaluated by an independent, trained radiologist who will not be involved in the study. Continuous epidural analgesia and intermittent intravenously administered analgesia (paracetamol or metamizol) will be introduced, and evaluated effective if a Numeric Pain Rating Scale (NPRS) score is lower than 3 points.

During postoperative care, continuous intraabdominal pressure (IAP) monitoring via a direct intraperitoneal catheter, placed before closure of the abdominal wall, will be performed to eliminate bias caused by the elevation of IAP.

Patients’ clinical progress and secondary endpoints will be monitored by daily SOFA scores, laboratory and physical examinations.

Postoperative hydration and vasopressor therapy will be directed by MAP, ScvO_2_, dCO_2_ and arterial lactate levels. PRBC units will be transfused if decreased hemoglobin (Hb) levels result in tissue oxygenation disorders or become symptomatic (hypotension, dizziness or weakness develop). Fresh frozen plasma will be given if the prothrombin International Normalized Ratio (INR) > 1.5. Platelet suspension units will be given according to the Transfusion Guidelines of the Hungarian National Blood Transfusion Service.

In both groups, patients will be allowed to drink clear fluids immediately after surgery and the use of chewing gum will be encouraged. Prokinetics and an oral liquid diet using a drinking formula will be started on POD 1 and patients will begin active mobilization. The nasogastric tube will be removed on the morning of POD 1.

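### The primary PPC outcome can be met by abnormal breathing sounds alone, which need not be new and are recorded by staff with no stated masking

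*Protocol article*

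**What the plan says.** Study endpoints gives PPC primary status: "The primary outcome variables are PPC and PCT kinetics". The definition is a list of alternatives. It starts with film findings (infiltrates or atelectasis, qualified as new), continues "abnormal breathing sounds on auscultation, respiratory failure defined as" a PaO2/FiO2 below 300, and closes "or the need for noninvasive or invasive ventilatory support within the first three postoperative days". No combination of items is required, and no criteria or severity threshold are given for breathing sounds. The word *new* stands before the film findings only.

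On who judges the outcome, the section on blinding says "This is a single-blinded (participant) study". Its one stated safeguard is that record forms are not completed in front of the patient. Postoperative care provides independence for one component: "The chest X-ray will be evaluated by an independent, trained radiologist who will not be involved in the study". That radiologist is not expressly said to be masked to allocation. A film is taken for everyone on the first postoperative day and then "repeated on the following days if the development of pulmonary complications are suspected". The adverse events section has daily visits by the intensive care therapist and urologist in charge, with a study nurse recording data. No passage names the person who auscultates.

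On baseline state, Selection of the participants excludes "history of severe chronic obstructive pulmonary disease (COPD, GOLD grades III or IV") and severe or uncontrolled asthma, so milder COPD and controlled asthma are eligible. A preoperative chest film is scheduled; the text mentions no preoperative auscultation.

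Objectives of the study puts oxygenation together with PPC as the first objective. Blood gases with PaO2/FiO2 are taken every 6 h to 72 h, but the only oxygenation measure among the endpoints is the cut at 300 inside the PPC definition.

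**The concern.** Auscultation is the most subjective of the listed components, and it carries the same weight as a film finding or a need for ventilatory support. Two things can follow.

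First, assessor bias. If the person listening to the chest knows which ventilation strategy was used, borderline sounds can be scored differently in the two arms, and the primary result moves without any true effect. The same knowledge could influence who gets a second film, although the scheduled first-day film limits this.

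Second, dilution. Sounds that were present before surgery, or that are trivial, add events to both arms alike. This needs no bias at all. It shrinks the contrast in a trial of 20 per arm that has little power to spare.

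**Working it through.** **Is the rule as described?** Three readings of the text settle this.

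1. The list is closed by an or, and no passage asks for two items together. On its plain reading, one item is enough.
2. *New* can cover both infiltrates and atelectasis, since both are film findings and a preoperative film exists for comparison. It does not extend to breathing sounds, which form a separate item.
3. Blinding is limited to the participant, and independent assessment to the film. The external physician under Data monitoring checks accuracy and completeness of records, which is not masked adjudication.

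**Inputs for the size.**
- From the protocol: 40 patients at 1:1, so 20 per arm (10 blocks of four = 40); significance at 0.05, taken as two-sided; Fisher's exact test, which Statistics names for proportions.
- Assumed, because the protocol gives no PPC rate, effect size or power: the true PPC rate p, and the share f of patients without a true PPC who are scored positive on auscultation alone.

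There is no stated power or event rate to reproduce.

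**Formula.** Observed rate = p + (1 − p) × f. Rejection rates are exact: all 21 × 21 possible outcomes are enumerated and weighted by their binomial probabilities.

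**Bias, no true effect.** p = 30% in both arms; f = 10% in the study group (SG), so its observed rate is 0.30 + 0.70 × 0.10 = 37%.

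| f in control group (CG) | Observed CG rate | Observed risk ratio SG/CG | Fisher rejection rate |
|---|---|---|---|
| 10% | 37% | 1.00 | 2.5% |
| 20% | 0.30 + 0.70 × 0.20 = 44% | 0.84 | 3.8% |
| 30% | 0.30 + 0.70 × 0.30 = 51% | 0.73 | 8.0% |
| 35% | 0.30 + 0.70 × 0.35 = 54.5% | 0.68 | 11.4% |
| 40% | 0.30 + 0.70 × 0.40 = 58% | 0.64 | 16.0% |

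For reference, equal f of 20% in both arms gives 2.2%. Fisher's test is conservative at this size, so the mild gap (10% against 20%) stays below the nominal 5%, although the observed risk ratio is already off 1.

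**Dilution, no bias.** With equal f in both arms, the risk difference is multiplied by (1 − f). Take a true 50% against 20%:

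| f in both arms | Observed rates, CG and SG | Risk difference | Fisher power |
|---|---|---|---|
| 0 | 50% and 20% | 30 points | 41% |
| 20% | 0.50 + 0.50 × 0.20 = 60% and 0.20 + 0.80 × 0.20 = 36% | 24 points | 21% |
| 30% | 0.50 + 0.50 × 0.30 = 65% and 0.20 + 0.80 × 0.30 = 44% | 21 points | 16% |

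Another assumed pair, 40% against 10%, behaves the same way: power falls from 49% to 24% at f = 20%.

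**The case against.** The strongest reply has five parts.

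*No passage says the auscultator is unblinded.* This stands. Ventilation is set in theatre and patients are examined later in the ICU or on the ward. A reader might infer from participant-only blinding that these staff know the allocation. That is plausible, but the text shows only that no masking is stated for them.

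*A postoperative complication implies new onset, and operational criteria may sit in the full protocol.* Partly fair. An article may leave auscultation criteria to a longer document, and the assessment schedule figure is not shown. But the definition does state novelty for the film and omits it for the sounds, so the rule as printed lets a pre-existing finding count.

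*The sizes depend on chosen rates.* This stands. Differential scoring of 10% against 35% is a strong scenario, which is why the range is shown. Some auscultation-only positives may also reflect real atelectasis, so treating them all as false gives the unfavourable end. Power is only 41% before any dilution, so much of the weakness comes from the sample size. Statistics also assigns PPC to an unpaired t test; Fisher's test is used here because PPC is read as a yes/no outcome.

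*The gas criterion is not shown to be loose.* A reader might infer that any single PaO2/FiO2 below 300 among the serial gases makes a PPC, and that a large share of patients would qualify that way. The protocol does not say whether one value or a sustained fall is meant, so no such share can be drawn from it.

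*The trial is running, and redefining a primary endpoint midway has its own risk.* This stands and shapes the fix. It is also why auscultation should not be made conditional on a film or gas criterion: either of those already qualifies alone, so the component would become redundant.

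**Conclusion.** The point holds as a cheap improvement to the PPC outcome. As written, abnormal breathing sounds alone make a primary event, need not be new although patients with mild or moderate COPD or controlled asthma can enter, and are recorded by staff with no stated masking.

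The direction of the dilution follows from the definition, once some sounds are old or trivial. Its size, and the whole of the bias, rest on assumed rates: a false-positive rejection rate between 3.8% and 16.0% over the scenarios shown, and roughly a halving of power or somewhat worse at false positives of 20 to 30%.

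A reader might go further and conclude that the primary result is biased. The documents do not support that. Knowledge of allocation by the assessor is inferred, the film has an independent reader and a scheduled first-day reading for everyone, PaO2/FiO2 and ventilatory support are more objective, and the other primary outcome, procalcitonin, is a laboratory value that this weakness does not touch.

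**What to change.** 1. Count breathing sounds only if they are new against a recorded preoperative examination.
2. Have the existing radiologist, and whoever records PPC, work without knowledge of allocation. The ventilation record stays available for care.
3. Before any data are analysed, prespecify a sensitivity analysis of PPC that excludes auscultation-only events, or report that component separately. For patients already enrolled without a recorded baseline examination, this is the part that still works.
4. Analyse PaO2/FiO2 over 72 h as a continuous secondary outcome, since oxygenation is a stated objective and the values are already collected every 6 h.

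The cost is a slightly lower PPC event rate, one recorded baseline auscultation per patient, some organisation to keep the recorder masked, and a little more analysis. No additional blood sample is needed. A change to the primary definition while recruitment is under way should be dated and justified without reference to outcomes by arm.

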#### Intraoperative care

Before induction of anesthesia an epidural catheter and an arterial cannula will be inserted for invasive arterial blood pressure monitoring and blood gas sampling.

Immediately after induction of anesthesia and orotracheal intubation, once a steady state has been reached (Table 2), all patients will be submitted to an ARM using the sustained airway pressure by the CPAP method, applying 30 cmH_2_O PEEP for 30 s. After ARM, PEEP will be set to 6 cmH_2_O in the CG (“standard PEEP”) and LPV (TV = 6 mL/Kg IBW, FiO_2_ = 0.5) will be performed. In the SG (“optimal PEEP”) PEEP will be determined during a Cstat-directed decremental PEEP titration procedure. During surgery ARM will be repeated and arterial and central venous blood gas samples (ABGs, CVBGs) will be evaluated every 60 min. In case of decreased oxygen saturation (SpO_2_ < 94%) rescue ARM will be performed using a FiO_2_ of 1.0. PCT levels will be measured 2, 6, 12, 24, 48 and 72 h after surgical incision.

**Table 2 Tab2:** Steady state after induction of anesthesia

	Parameter	Value
Hemodynamics	Mean arterial pressure	65 mmHg < MAP < 90 mmHg
	Heart rate	50/min < HR < 100/min
Ventilation	SpO_2_	≥96%
	EtCO_2_	35–40 mmHg
Anesthetics	EtSevo	1.0 MAC

*MAP* mean arterial pressure, *HR* heart rate, *SpO*
_*2*_ peripheral capillary oxygen saturation, *EtCO*
_*2*_ end-tidal carbon dioxide partial pressure, *EtSevo* end-tidal sevoflurane concentration, *MAC* minimal alveolar concentration

Arterial blood pressure, heart rate (HR) and end-tidal carbon dioxide tension (EtCO_2_) will be monitored continuously. Cstat, airway resistance (Raw), Vds/Vt, core temperature and train-of-four relaxometry data will be recorded every 15 min.

During surgery, in cases of hypotension, intravenous norepinephrine will be started to maintain mean arterial pressure above 65 mmHg. For intraoperative fluid management patients will receive 3 mL/Kg/h of balanced crystalloid solution until end of surgery. In cases of bleeding, a 200-mL colloid (hydroxyethyl starch, HES) solution bolus and crystalloid substitution will be given. Packed red blood cell (PRBC) transfusion will be given whenever the attending anesthetist feels it necessary.

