### Adverse events and interruption of the trial

Every patient included in the trial will receive daily visits from an intensive care therapist and urologist in charge from POD 1 until leaving the hospital. During ICU stay, and if necessary on the intermediate care unit, all patients will be continuously monitored. The study nurse will be responsible for collecting blood samples and will record relevant required data onto CRF. During the out-of-hospital follow-up period (until POD 28) patients’ progress, particularly deterioration will be checked by daily phone-call visits.

The investigators will monitor the patients for any adverse events (AEs), which are defined as severe or prolonged hypotension (systolic blood pressure < 90 mmHg) and significant cardiac arrhythmias associated with the PEEP titration procedure. AEs will be documented on the CRF and the principal investigator will be informed.

Serious adverse events (SAEs) are defined as severe barotrauma leading to pneumothorax, significant prolongation of hospitalization, persistent or significant disability or incapacity, and severe deterioration (life-threatening state or even death) associated with the PEEP titration procedure. All treatment-related SAEs will be recorded and reported to the Hungarian Scientific and Medical Research Council Ethics Committee and the Local Ethics Committees. If any SAEs occur, the trial will be interrupted and an investigation will be performed.

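### The severe-arrhythmia rule in Table 1 reduces to HR > 150/min and never counts bradycardia; two blood-gas criteria carry a 28-day frame although their scheduled sampling ends at 72 h

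*Protocol article*

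**What the plan says.** Under Study endpoints, Table 1 of the protocol article lists five groups of secondary endpoints, each with a time frame. The first is "Circulatory failure 28 days", with ten criteria beneath it. The line for severe cardiac arrhythmia reads "40/min < HR > 150/min". Two other lines are ScvO2 below 70% and dCO2 above 7 mmHg. The remaining lines are a pressure criterion, lactate, bicarbonate and four clinical events: acute coronary syndrome, acute left ventricular failure, pulmonary embolism and cardiac arrest.

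Under Intraoperative care, Table 2 writes a heart-rate range in the ordinary way: "50/min < HR < 100/min".

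Under Postoperative care, arterial and central venous blood gases are collected, and the derived values "will be calculated every 6 h until 72 h after surgery". That section also has the secondary endpoints followed by daily SOFA scores, laboratory tests and physical examination, with no stated end. The section on POD 4 to POD 28 says that secondary endpoints are evaluated during follow-up. Under Adverse events and interruption of the trial, patients are visited daily until discharge. After discharge, progress and "particularly deterioration will be checked by daily phone-call visits" up to POD 28.

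**The concern.** Table 1 is where the trial fixes what counts as a circulatory event when the two arms are compared. A rule that cannot register a slow heart rate gives a one-sided arrhythmia count if it is applied as printed. The adverse-event section does not fully make up for this. It captures significant arrhythmias linked to the PEEP titration procedure, and only the study group undergoes that procedure, so it does not give a like-for-like comparison.

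The time frame raises a separate problem. ScvO2 and dCO2 can be known only from a central venous sample, with an arterial sample as well for dCO2. Up to 72 h both arms are sampled on the same timetable. After that, a value exists only if the patient is still in hospital and someone takes a sample. The Background section expects the intervention to shorten hospital stay. If it does, study-group patients have less time in which these two abnormalities can be seen, and their apparent event rate falls for a reason unrelated to circulation.

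**Working it through.** The plan states no figure to reproduce here. The check is one of logic and of comparing sections.

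**Heart-rate rule.** Input: the Table 1 criterion, 40 < HR > 150.

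1. A chained inequality means that both parts hold: (HR > 40) and (HR > 150).
2. Any rate above 150 is also above 40, so the pair is equivalent to HR > 150.
3. Tested on every integer rate from 0 to 250:
   - As printed, the rule is true from 151 to 250 only, and is identical to HR > 150.
   - Rates below 40 counted as printed: 0 of 40 (0 to 39).
   - Rates below 40 counted under HR < 40 or HR > 150: 40 of 40. Rates of 151 and above are counted as before.
4. Changing a sign does not repair it. 40 > HR > 150 asks for a rate both below 40 and above 150, which no rate meets. 40 < HR < 150, the form used in Table 2, would count ordinary rates as events. Two tails need two separate conditions joined by *or*.

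**Time frame of ScvO2 and dCO2.** Inputs: 28 days (Table 1); blood gases every 6 h to 72 h (Postoperative care); telephone contact after discharge (Adverse events section).

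1. Scheduled window: 72 h / 24 = 3 days.
2. Share of the stated frame: 3 / 28 = 0.107, or 11%. This is a share of calendar days, not an estimate of events missed.
3. The sources of information over the 28 days are:

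| Period | ScvO2 and dCO2 | Clinical events |
|---|---|---|
| To 72 h after surgery | Scheduled every 6 h, both arms | Observed in hospital |
| After 72 h, still in hospital | No schedule stated in the text; found only if sampled | Daily visits |
| After discharge, to POD 28 | Not obtainable by telephone | Can be asked about by telephone |

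4. For the two blood-gas lines, only the first row is comparable by design. The later rows depend on length of stay, and ICU days and hospital stay are both tertiary endpoints.

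The documents give no expected event rates or lengths of stay, so the size of any resulting bias cannot be calculated.

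**The case against.** The strongest reply on heart rate is that this is a slip of notation. A limit of 40 serves no purpose unless rates below it count, so the two-sided intent is fairly plain, and Table 2 shows that the authors can write a range correctly. Staff may well have applied the intended rule. That stands as an account of the likely cause. It does not make the printed rule usable, and nothing in the article states the intended one.

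On the time frame, the reply is that the protocol does follow secondary endpoints beyond 72 h, through daily laboratory and physical examinations, daily visits until discharge, evaluation from POD 4 to POD 28 and daily calls. This stands for the endpoint as a whole. A reader might infer that circulatory failure is measured only to 72 h, and the text contradicts that. The limit belongs to the scheduled blood gases. Nor do the documents support cutting the pressure criterion to 72 h, since no such limit on pressure is stated. The SPIRIT schedule in Figure 1 was not available for this check and could list further sampling times.

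A reader might also infer that vasopressors mask the hypotension line, "Hypotension – MAP < 65 mmHg", because "intravenous norepinephrine will be started to maintain mean arterial pressure above 65 mmHg". The line has no vasopressor term, but that sentence starts treatment in response to hypotension, and nothing says that the triggering episode goes uncounted. Masking is therefore not shown.

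Finally, it would be too strong to say that the definition hides haemodynamic harm. Nine other criteria remain, and the adverse-event definition of arrhythmia has no rate limits, so bradycardia can be recorded there.

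**Conclusion.** The point holds in two parts. The heart-rate criterion is wrong as printed: it equals HR > 150/min and counts no rate below 40/min. This follows from the text alone and needs no assumption. Its practical effect depends on whether the rule is applied literally, and on whether an affected patient meets another of the ten lines.

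The ScvO2 and dCO2 lines have a stated schedule for 3 of their 28 days. After that, detection depends on length of stay. This assumes that the unseen schedule figure adds no later sampling. A bias in favour of the study group would also require that the intervention does shorten stay, as the trial hopes; its size is unknown.

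Both defects lie in one composite secondary endpoint. They should be corrected before analysis, but they do not touch pulmonary complications or procalcitonin, the primary endpoints.

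**What to change.** Make two changes to Table 1.

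1. Write the arrhythmia criterion as HR < 40/min or HR > 150/min. This keeps both printed limits and changes only how they are joined; whether they are the right limits is not a question for this review. The cost is one line.
2. Give ScvO2 and dCO2 a time frame of 72 h after surgery, matching their scheduled sampling in both arms. Keep 28 days for acute coronary syndrome, left ventricular failure, pulmonary embolism and cardiac arrest. No new data are needed, because these samples are already scheduled. The cost is that blood-gas abnormalities after 72 h no longer count towards the endpoint; they can be listed descriptively by arm.

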On the one hand major abdominal surgery induces an inflammatory response that is necessary for postoperative recovery (e.g., wound healing), but on the other hand an overwhelming inflammatory response may also lead to adverse events (AEs) such as organ dysfunction [15–19]. Radical cystectomy is considered major surgery; hence, there is an increased risk of postoperative complications. Inappropriate mechanical ventilation during general anesthesia can also lead to an amplified inflammatory response, which theoretically may worsen the postoperative outcome via several mechanisms. However, the relationship between LPV and the postoperative inflammatory response after radical cystectomy has not been investigated yet.

There is strong correlation between the degree of inflammatory response and serum procalcitonin (PCT) concentrations [20, 21]; hence, there is some rationale in the belief that monitoring the inflammatory response by regular PCT measurements in the postoperative period reflects the host response. Therefore, there is some rationale in monitoring PCT kinetics as an indicator of the host inflammatory response.

The aim of this investigator-initiated, double-center, single-blinded (subject), prospective, randomized controlled trial is to evaluate the effects of intraoperative LPV, applying an individually titrated optimal PEEP, on postoperative pulmonary complications (PPC) and the inflammatory response in patients undergoing radical cystectomy and urinary diversion (ileal conduit or orthotopic bladder substitute). We hypothesized that optimizing intraoperative mechanical ventilation (incorporating LPV, ideal PEEP and ARM) can attenuate the inflammatory response as compared to conventional modes of mechanical ventilation, and hence may result in improved postoperative oxygenation, prevent the occurrence of VILI, and reduce the incidence of organ dysfunction. These anticipated advantages may also improve postoperative recovery and survival rates, shorten in-hospital stay and reduce health care-related costs.

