#### From postoperative day 4 (POD 4 to POD 28, follow-up)

During the follow-up period, secondary endpoints, in-hospital stay, 28-day and in-hospital mortality will also be evaluated.

Figure 2 shows the CONSORT flowchart of the trial.

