### Statistics

Data will be analyzed by the research team in collaboration with a medically versed biostatistician after completion of the trial. There will be no interim analysis. Statistical analysis will be conducted on an intention-to-treat basis. IBM SPSS 20.0 statistical software will be used for analysis.

It is expected that the majority of source data will be recorded onto CRF; nonetheless, before starting the data analysis, the mechanism and pattern of missing data will be evaluated and these findings will be used to determine whether they have had an impact on the statistical analysis and results and how they can be managed.

Data distribution will be tested by the Kolmogorov-Smirnov analysis. Normally distributed data will be presented as mean and standard deviation (SD) and skewed data as median (interquartile range). Comparing related samples, the paired and unpaired *t* test will be used for normally distributed data and the Wilcoxon signed rank test and Mann-Whitney *U* test for skewed data. Differences in proportions will be evaluated using the Fisher’s exact test, and risk ratio with associated 95% confidence interval (CI). Analysis of the primary endpoint (PPC) will be carried out by the unpaired Student’s *t* test (95% CI). A two-way, repeated-measures analysis of variance (two-way RM ANOVA) will be used to compare the groups’ serum PCT levels. The relationship between PCT levels and organ dysfunctions will be evaluated using the Pearson correlation. Statistical analysis of SOFA scores, ICU days, in-hospital stay, in-hospital and 28-day mortality data of groups will be implemented by the chi-square test. A *P* value < 0.05 will be considered significant.

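### ICU days and in-hospital stay are raw durations with mortality kept apart, so an early death counts as a short stay and reads as benefit

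*Protocol article*

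**What the plan says.** All places are in the protocol article; no separate statistical analysis plan is shown.

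- **Study endpoints** sets the third tier: "Tertiary endpoints are intensive care unit (ICU) days, in-hospital stay, in-hospital and 28-day mortality". The two durations have no qualifier such as alive, or among survivors, and death is its own item.
- **Statistics** commits to intention to treat, so patients who die stay in the comparison. It assigns one test to the whole group: "Statistical analysis of SOFA scores, ICU days, in-hospital stay, in-hospital and 28-day mortality data of groups will be implemented by the chi-square test". No rule for deaths is attached. On missing data it says that "before starting the data analysis, the mechanism and pattern of missing data will be evaluated".
- **Background** gives the direction in which stay will be read: "These anticipated advantages may also improve postoperative recovery and survival rates, shorten in-hospital stay and reduce health care-related costs". The Discussion again treats less time in hospital as a gain.
- **From postoperative day 4** adds: "During the follow-up period, secondary endpoints, in-hospital stay, 28-day and in-hospital mortality will also be evaluated".

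**The concern.** Time in ICU or hospital ends in one of two ways, discharge or death. A raw duration does not tell them apart, so an early death takes a value at the short end of a scale on which short is good. When mortality is a separate endpoint, nothing in the stay endpoint corrects for this.

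The missing-data review would not clearly catch it. A patient who dies on POD 2 has a fully observed stay, and no value is missing.

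Unequal deaths cannot be excluded in advance. The section on adverse events includes death associated with the PEEP titration procedure among serious adverse events, and only the study group undergoes titration. This does not show that more deaths are expected there. It shows that the protocol allows for a harm tied to one arm, and the stay endpoints as defined would credit that arm for it.

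**Working it through.** **Inputs from the article.** 40 patients, allocated 1:1, in 10 blocks of four: 10 × 4 = 40, so 20 per arm. No figure for mortality, ICU days or length of stay is given, so there is none to reproduce.

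**Assumptions (not in the article).** Survivor mean stay μ of 10, 14 or 20 days; death on day d = 2 or d = 5; k deaths in an arm.

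**Step 1: effect on an arm's mean raw stay.** With k deaths and 20 − k survivors,

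mean = [(20 − k)μ + k·d] / 20 = μ − k(μ − d)/20.

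The shift is therefore −k(μ − d)/20. For k = 1:

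| Survivor mean μ | Death on day 2 | Death on day 5 |
|---|---|---|
| 10 days | −8/20 = −0.40 | −5/20 = −0.25 |
| 14 days | −12/20 = −0.60 | −9/20 = −0.45 |
| 20 days | −18/20 = −0.90 | −15/20 = −0.75 |

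For k = 2 each entry doubles, giving −0.50 to −1.80 days. Every shift is towards a shorter stay. One death in one arm and none in the other puts the full shift into the difference between arms. The same death in both arms, with the same survivor mean, cancels.

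**Step 2: how often a death would occur.** The chance of at least one death among 40 is 1 − (1 − q)^40.

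| Assumed mortality q | Expected deaths (40q) | Chance of at least one |
|---|---|---|
| 1% | 0.4 | 33% |
| 3% | 1.2 | 70% |
| 5% | 2.0 | 87% |
| 10% | 4.0 | 98% |

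These are upper limits for this purpose. Only a death earlier than the usual discharge day shortens stay; from Step 1, a death with d > μ lengthens the arm's mean.

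**Step 3: the planned test.** Chi-square is assigned to ICU days and stay, so the mean shift describes the direction and size of the distortion and is not the planned test statistic. If stay is grouped into categories for that test, an early death falls in a short-stay category and the direction is unchanged.

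**Step 4: the alternative measure.** Assume every survivor is discharged by POD 28 and not readmitted, with stay counted from surgery. A survivor with stay s then scores 28 − s, and a death scores 0. One death shifts the arm's mean by −(28 − μ)/20:

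- μ = 10: −18/20 = −0.90
- μ = 14: −14/20 = −0.70
- μ = 20: −8/20 = −0.40

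Fewer days is worse on this scale, so the death now counts against its arm.

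**The case against.** The strongest reply is that the article is silent. It nowhere says that a death is scored as a short stay, and a fuller protocol or an analysis plan may hold a rule. That stands as a limit: the point rests on the literal reading of the endpoint definition. It does not remove the point, because what a duration endpoint measures is part of its definition, and the article gives that definition as a plain duration under intention to treat.

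It also stands that these are tertiary endpoints, that both mortality endpoints sit in the same tier so an imbalance would be visible, and that the bias needs unequal early deaths.

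A reader might infer two stronger points, which the article does not support.

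- **That an early death would pass as free of postoperative pulmonary complications (PPC), a primary endpoint.** Death is not among the listed components: "PPC are defined as new infiltrates or atelectasis on a chest X-ray, abnormal breathing sounds on auscultation, respiratory failure defined as" a PaO2/FiO2 threshold, or "the need for noninvasive or invasive ventilatory support within the first three postoperative days". But Postoperative care has PaO2/FiO2 calculated every 6 hours to 72 hours and a chest X-ray on POD 1, and ventilatory support already counts. The problem needs a death within three days with no component recorded first. At an assumed 72-hour mortality of 0.25% to 1%, 0.1 to 0.4 such early deaths are expected among 40, and most would probably already be PPC cases. Adding all-cause death to a pulmonary primary endpoint is a debatable trade-off, since a death from bleeding would count as pulmonary.
- **That observation of inpatients stops at POD 28, cutting off long stays and missing later in-hospital deaths.** The follow-up heading ends at POD 28, but the section on adverse events has daily visits until the patient leaves hospital. It attaches the POD 28 limit to telephone follow-up after discharge.

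**Conclusion.** The point holds for ICU days and in-hospital stay only. As defined, an early death enters as a short duration that the article reads as benefit, and unequal early deaths would favour the arm with more of them. For hospital stay, one such death lowers the mean of a 20-patient arm by about 0.25 to 0.90 days, assuming death on day 2 to 5 and a survivor mean stay of 10 to 20 days. No mortality or stay figure in the article can narrow that range, and the article gives no reason to expect the imbalance in a particular direction. It is a minor improvement to tertiary endpoints, and it does not challenge the primary PPC comparison.

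**What to change.** Replace the two raw durations with days alive and out of ICU, and days alive and out of hospital, both from surgery to POD 28, with death by POD 28 scored 0. State whether readmission days are subtracted. Compare the arms with a rank test or another method suited to a numeric outcome, in place of chi-square. Report raw ICU days and raw stay in survivors beside it, descriptively, and keep both mortality endpoints as they are.

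Stay, ICU days and 28-day mortality are already endpoints, and discharged patients are telephoned daily to POD 28, so no new data collection is evident. As the trial is registered and ongoing, the change should be recorded as a dated amendment before the outcome data are analysed.

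The downside is small: the measure combines survival and stay, and a patient still in hospital at POD 28 scores the same 0 as one who died. The survivor stay and mortality figures shown beside it let a reader separate the two.
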